### Outcomes

The efficacy of Wangbi granule will be observed and the main outcome is DAS28 [19], assessed by a dedicated rheumatologist (associate senior physician or better). The changes in the DAS28 score will be recorded during the observation period. Moreover, participants are considered to have achieved deep clinical remission when the calculated DAS28 score is lower than 2.6.

Secondary outcomes include patient-reported outcomes (symptom score) [18], ACR50 [20], fatigue scale-14 (FS-14) [21], visual analogue scale for pain (VAS) [22], health assessment questionnaire disability index (HAQ-DI) [23] and biological markers [24] such as CRP and ESR. Specific secondary outcomes are shown in Table 3.

**Table 3 Tab3:** Secondary outcomes of the trial

Secondary outcomes	
ACR50	ACR response was used to evaluate improvement in RA. ACR response requires the collection of the degree of improvement in the number of joints with pressure pain and the degree of improvement in the number of joints with swelling and the degree of improvement in 3 of the following 5 items: patient’s assessment of pain, patient’s overall assessment of disease activity, physician’s overall assessment of disease activity, patient’s assessment of physical function (HAQ), and values of acute phase reactants (ESR, CRP). Percentage improvement in each indicator = (pre-treatment value − post-treatment value)/pre-treatment value * 100% ACR20: ≥ 20% improvement in joint pain and swelling, and ≥ 20% improvement in at least 3 of the other 5 items ACR50: ≥ 50% improvement in joint pain and swelling, and ≥ 50% improvement in at least 3 of the other 5 items ACR70: ≥ 70% improvement in joint pain and swelling, and ≥ 70% improvement in at least 3 of the other 5 items
VAS	Patients’ joint pain levels were evaluated using the VAS, expressed on a ten-point scale, with higher scores indicating more intense pain Face-to-face or telephone follow-ups were conducted at baseline, 4 weeks, 8 weeks, and 12 weeks of treatment, and patients were scored based on their subjective perceptions
FS-14	FS-14 is used to measure the patient’s fatigue level. FS-14 was divided into 2 dimensions: physical fatigue (8 items) and mental fatigue (6 items). The scoring method is based on a 2-point scale, with 0 points for “No” and 1 point for “Yes”, and reverse scoring for items 10, 13 and 14, with a total score of 0 to 14 points, with higher scores representing heavier fatigue Face-to-face or telephone follow-ups were conducted at baseline, 4 weeks, 8 weeks, and 12 weeks of treatment, and patients were scored based on their subjective perceptions
HAQ-DI	The HAQ-DI was used to assess the overall functional status of the patients. The questionnaire consists of 20 questions containing 8 areas of daily activity, with higher scores on each question representing poorer functioning Face-to-face or telephone follow-ups were conducted at baseline, 4 weeks, 8 weeks, and 12 weeks of treatment, and patients were scored based on their subjective perceptions
Symptom score	The patient’s symptoms associated with RA were recorded, including joint swelling, pressure pain, activity level, diet, etc. The greater the degree of performance of each symptom, the higher the score Face-to-face or telephone follow-ups were conducted at baseline, 4 weeks, 8 weeks, and 12 weeks of treatment, and patients were scored based on their subjective perceptions
Biological markers	All patients will have their venous blood and other required specimens collected on an empty stomach in the early morning of the specified date and tested in the testing department of each research center, and the biological samples will be frozen in a special refrigerator in China-Japan Friendship Hospital Routine blood, urine, and stool tests were performed at baseline, 4 weeks, and 12 weeks of the trial Electrocardiograph, ALT, AST, and serum creatinine were tested at baseline, 4 weeks, and 12 weeks of the trial to monitor the safety of drug administration ESR and CRP were measured at baseline and 12 weeks of the trial to monitor inflammation levels RF and ACPA were tested during the baseline period of the trial to determine the patient’s antibody levels Additional blood samples were collected at baseline, week 12 of the trial and used to test for various proteins and genes such as inflammatory cytokines

*ACR50* American College of Rheumatology 50% response criteria, *VAS* visual analogue scale for pain, *FS-14* fatigue scale-14, *HAQ-DI* health assessment questionnaire disability index, *ALT* alanine aminotransferase, *AST* aspartate aminotransferase, *ESR* erythrocyte sedimentation rate, *CRP* C-reactive protein, *RF* rheumatoid factors, *ACPA* anti-citrullinated protein antibodies

### Safety

Medications including methotrexate, tofacitinib, and Wangbi granule are all commonly used for RA and are not expected to cause unacceptable side effects compared to their therapeutic effects. If an adverse reaction is suspected, treatment will be stopped immediately with the permission of the Principal Investigator. During the trial period, investigator will provide participants with free trial drugs. Participants will have access to some free tests and receive a set amount of subsidy.

An adverse event is defined as any adverse medical event that occurs between the time the participant signs the informed consent and the last follow-up visit, whether or not it is causally related to the study drug. Adverse events will be monitored continuously during the treatment period, regardless of whether adverse events are related to the trial drug, the investigators should fill out the record form truthfully and in detail. A serious adverse event, such as a new or previous exacerbation of the patient’s disease during treatment, must be reported within 24 h. Termination of the trial should be considered when additional immunosuppressive drugs or other medications, surgery or other physical therapy associated with the improvement of RA are indeed required. Such a sample will be treated as an off-case. The study team will continue to track the progress of adverse events.

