Participants may decide to withdraw from the trial at any time for any reason of their own choosing. The investigators may also ask the participant to withdraw from the trial for rational reasons. All participants who have completed the informed consent form and are screened and qualified to enter the randomized trial, regardless of when and why they withdrew, will be treated as dislodged cases as long as they do not complete the observation period specified in the protocol.

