### Statistical analysis

All analysis and data visualization will be performed using IBM SPSS (Version 25.0), R (Version 4.1.1).

Baseline data will be displayed using descriptive statistics (eg, means, SD, median, IQR, proportions). We will test the group balance achieved by randomization through appropriate statistical tests (eg, Student’s t tests, Pearson’s χ^2^ tests). Outcomes with a continuous distribution will be compared between groups using the mean (Student’s t test) and Pearson’s χ^2^ test will be used for binary categorical data where categorical variables are expressed as frequencies and percentages and continuous variables are expressed as means and SD.

Preliminary statistical analysis of the primary outcome data will be performed according to the intention-to-treat principle, and the changes in DAS28 will be compared between patients treated with Wangbi granule and Wangbi placebo, and report the rate of deep remission. Further, two-way repeated measures analysis of variance (ANOVA) will be used to examine any interaction effects of the outcome variables between the two groups at the four time points. Mauchly’s sphericity test will be used to examine the spherical assumptions of the repeated measures ANOVA. Bonferroni-corrected post hoc multiple comparisons will be used to examine simple effects between groups at different time points and at different time points for each group.

Sensitivity analysis will be an essential part of the statistical analysis process to complement the interpretation of the results. Depending on the specifics of the data, the full samples will be divided into subgroups based on information about additional drugs (e.g. NSAIDs), co-existing underlying conditions (e.g. hypertension, diabetes), long-term use of other drugs, etc. The calculations will be re-run in each subgroup to verify the validity of the results. When necessary, a per protocol set (PPS) analysis will be part of the sensitivity analysis. If any variable has no more than 20% missing values, the MICE package in R will be used for multiple interpolation to replace it. For the statistical process, *P* < 0.05 is considered statistically significant.

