### Data management

Investigators and participants obtain the required information in person or by telephone, and investigators will consult the hospital’s medical records system to complete additional details. All the data obtained are recorded in the special paper case report form. The information obtained from the last recording will be used as the final data for participants who withdrew. After the CRO collects the paper documents returned by each research center, these data are stored in a special database for unified management. Epidata software will be used to establish the corresponding database, and the data will be entered synchronously by different data managers, using the two-entry method. The CRO will be in charge of data management. The biological sample are stored in the bio-sample bank of China-Japan Friendship Hospital.

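### Two unranked rules can fill the week-12 DAS28 of withdrawn participants, and those who need added RA therapy probably lose the observed value

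*Protocol article*

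**What the plan says.** Four parts of the protocol article bear on a participant who needs more RA treatment before week 12.

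- **Safety.** "Termination of the trial should be considered when additional immunosuppressive drugs or other medications, surgery or other physical therapy associated with the improvement of RA" prove necessary. The next sentences read "Such a sample will be treated as an off-case" and "The study team will continue to track the progress of adverse events". No other follow-up after termination is mentioned.
- **Eligibility criteria (withdrawal paragraph).** "The investigators may also ask the participant to withdraw from the trial for rational reasons". Randomised participants, "regardless of when and why they withdrew, will be treated as dislodged cases as long as they do not complete the observation period", so every non-completer falls into one class.
- **Data management.** "The information obtained from the last recording will be used as the final data for participants who withdrew".
- **Statistical analysis.** "Preliminary statistical analysis of the primary outcome data will be performed according to the intention-to-treat principle", with the deep-remission rate also reported. For gaps in the data: "If any variable has no more than 20% missing values, the MICE package in R will be used for multiple interpolation to replace it".

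The Interventions section separately allows low-dose NSAIDs for unbearable pain, with all off-protocol drug use recorded. That permitted use is not at issue here.

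**The concern.** A need for additional RA therapy is closely tied to the primary outcome, so these participants are likely treatment failures. An intention-to-treat comparison depends on observing them. The Safety wording points the other way: consider ending participation, label the case as off, and keep following adverse events.

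Once the week-12 DAS28 is absent, two rules can supply it, and they do different things. Last-recording carry-forward inserts an earlier score as if it were the week-12 score. Multiple imputation draws plausible values from a model and carries their uncertainty into the result. One value cannot be handled both ways in the same analysis, and nothing in the article makes one rule primary and the other a sensitivity analysis.

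At stake are the between-arm DAS28 difference and the deep-remission rate. Under carry-forward, a participant who scored below 2.6 at week 4 or week 8 and then worsened enough to need other therapy could be counted as a remission.

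**Working it through.** **1. Planned loss.** Inputs from Sample size calculation: 155 per group before loss, 10% shedding, 170 per group, 340 in total. Reproducing the inflation: 155 × 1.10 = 170.5 and 155 / 0.90 = 172.2, so the stated 170 is close to either convention. Planned loss is 0.10 × 340 = 34, or 17 per arm. Subtraction gives a similar figure: 2 × (170 − 155) = 30.

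**2. Does the multiple-imputation rule apply at that loss?** Its limit is 0.20 × 340 = 68 missing values. Both 30 and 34 are below 68, so it does. It covers any variable and makes no exception for withdrawals. The last-recording rule covers every participant who withdrew. At the planned loss both can reach the same week-12 DAS28.

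**3. Which rule would act first?** The article does not say. If the last recording is entered as final data during data management, the value is no longer missing when the imputation rule is applied, and carry-forward prevails by order of processing. If the value is left blank, imputation prevails. The result would then depend on a database step.

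**4. Can a carried value create a false remission?** Entry requires DAS28 of 2.6 to 3.2; deep remission is a score below 2.6 (Outcomes).
- A carried baseline value is at least 2.6, so it cannot count as remission.
- A carried week-4 or week-8 value can be below 2.6, so it can.
- A DAS28 taken when the new therapy is added already shows the worsening, and the problem shrinks.

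**5. Size per case, deep-remission rate.** One wrongly carried remission moves an arm's rate by 1/170 = 0.59 percentage points. A net excess of k such cases in one arm moves the difference by k × 0.59 points, in the direction set by that arm. The article gives no basis for choosing k.

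**6. Size, mean DAS28 (illustration only).** Let d_W and d_P be the proportions of off-cases on Wangbi and placebo, and x the amount by which the true week-12 score exceeds the carried one. Carry-forward shifts the difference (Wangbi minus placebo) by −(d_W − d_P) × x. The values below are assumed; none is in the article.

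| d_W | d_P | x = 0.3 | x = 0.6 | x = 1.0 |
|---|---|---|---|---|
| 10% | 10% | 0 | 0 | 0 |
| 5% | 15% | +0.03 | +0.06 | +0.10 |
| 15% | 5% | −0.03 | −0.06 | −0.10 |

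A positive shift hides benefit and a negative one exaggerates it. For scale, the planned difference is 0.5 points.

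**The case against.** Several points on the other side have force.

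- **The two rules can be read together.** The last-recording rule is specific to withdrawals and the imputation rule is general, so the first could govern withdrawals and the second sporadic gaps. A reader might infer a flat contradiction; the documents do not support that. What stands is that the article never states this division. If it is the intended one, carry-forward governs exactly the outcome-related exits, which is the less favourable choice.
- **Carry-forward of the endpoint is itself a reading.** The sentence sits under Data management and names neither DAS28 nor week 12. It might only mean that the last completed record closes the case report form. That is possible, but the words describe final data without limiting them.
- **Termination is discretionary, and loss of DAS28 is not stated.** A reader might infer that every rescued participant is removed, or is dropped from the intention-to-treat analysis. The text says neither. The planned re-analysis by additional drugs even implies that some participants with added medication stay in the data. Loss of the week-12 value is an inference from termination, off-case status and the mention of adverse-event tracking alone.
- **The analysis plan may settle it.** Only a condensed article is at hand. A plan could rank the two rules, although choosing imputation would override a sentence printed here. No plan can recover assessments that were not made.
- **The harm scenario is narrow.** It needs early remission followed by a flare before week 12. Week 8 is a telephone visit where Table 4 schedules DAS28 but not ESR/CRP, so a usable week-8 score is uncertain. If it is unusable, however, the carried value comes from week 4 or baseline, further from the endpoint.

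The subgroup re-analyses and the per-protocol analysis are partial safeguards, but neither restores a missing week-12 score.

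**Conclusion.** The point holds in a limited form and should be fixed. The article states two rules that can both reach a withdrawn participant's week-12 DAS28 at the planned loss (34 against a limit of 68) and does not say which governs. Its off-case wording makes it probable, though not certain, that likely treatment failures are not assessed at week 12. Under the last-recording rule, a score that may predate the worsening would then replace the missing one.

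A reader might go further and conclude that the trial is biased towards Wangbi, or by a known amount. The article gives no rescue or off-case rate, no split by arm, and no gap between carried and true scores; the 10% is loss from all causes. Equal exits with equal gaps cancel, and the sign follows whichever arm has more of them. The only firm unit is 0.59 percentage points of an arm's deep-remission rate per wrongly carried remission. Confidence is medium, because the conclusion rests on reading the last-recording sentence as applying to the endpoint and on inferring that DAS28 collection stops.

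**What to change.** 1. **Data management:** remove last-recording carry-forward for the week-12 DAS28. Use the multiple imputation already planned under Statistical analysis for values that are truly missing.
2. **Safety:** replace the off-case sentence with wording such as: added RA therapy may end study drug, but the assessments in Table 4 continue unless the participant withdraws consent. Analyse these observations by intention to treat.
3. **Statistical analysis:** add a sensitivity analysis that counts as not in deep remission anyone who, before week 12, started any therapy named in the Safety trigger: an immunosuppressive or other RA-improving drug, surgery or physical therapy. Exclude the low-dose NSAIDs that Interventions permits.

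The cost is a wording amendment, site retraining, and attendance by some participants off study drug at visits already scheduled. No new patients or procedures are needed. The main drawback is that an observed week-12 DAS28 will include the effect of the added therapy and can mask failure; the third change is there to show how much that matters. The change should be made before such exits occur, since unmeasured scores cannot be recovered.

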### Allocation and blinding

A central randomization system will be applied in this study, with an independent contract research organization (CRO) implementing the randomized assignment and drug dispensing in each subcenter. Participants will be randomized to either the intervention or control group, and stratified block group randomization will be used for participant randomization. In the random assignment process, participants are first allowed to enter the zone group and then are randomly allocated. The length of the zone group is set to 4, and the six permutations obtained are designated as AABB, ABAB, ABBA, BAAB, BABA, BBAA, with A and B representing the intervention or control group, whose exact meaning is known only to the designer. Subsequently, a string of random numbers is generated by SPSS software, and the allocation sequence is obtained by selecting numbers between 1 and 6 and arranging the district groups in the order of random numbers. Once each subcenter has determined the eligibility of participants and obtained the written consent to participate in the trial, a number will be requested from the randomization manager. The complete sequence of generated assignments is kept at the CRO, and the designer will place them in sequentially numbered sealed opaque envelopes and store them in a locked cabinet.

Researchers, participants and statistical analysts will be blinded to group assignment. After all cases are included, all clinical data will be entered into the database and verified, and the data will be locked after confirmation of accuracy. Groups A and B will be divided into two groups at the first unblinding, but it is not clear which group is the intervention group. After the statistical analysis, the results will be processed and the second unblinding will be carried out to find out whether group A and group B represent the intervention group or the control group. If a serious adverse event or unexpected adverse reaction occurs during the trial, the patient’s blinding status will be broken with the consent of the Principal Investigator (PI), and all such cases will be reported to the Clinical Research Ethics Committee of the China-Japan Friendship Hospital.

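### The code-break trigger is a category of event that includes disease exacerbation, so worsening RA can by itself qualify a patient for unblinding; the fixed block length of 4 adds a small secondary leak

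*Protocol article*

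**What the plan says.** Two sections of the protocol article bear on this.

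- **Allocation and blinding.** Researchers, participants and analysts are to be blinded. The exception reads: "If a serious adverse event or unexpected adverse reaction occurs during the trial, the patient’s blinding status will be broken". The sentence goes on to require the Principal Investigator's consent and a report of all such cases to the ethics committee. It does not say on what ground consent is given or refused.
- **Safety.** "A serious adverse event, such as a new or previous exacerbation of the patient’s disease during treatment, must be reported within 24 h". This is the section's only example of a serious adverse event.

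On the allocation list, the article says that "stratified block group randomization will be used for participant randomization", without naming the strata. It also fixes the block: "The length of the zone group is set to 4, and the six permutations obtained are designated as AABB, ABAB, ABBA, BAAB, BABA, BBAA". On custody: "The complete sequence of generated assignments is kept at the CRO".

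The primary outcome is DAS28, assessed by a dedicated rheumatologist (Outcomes). The primary analysis follows the intention-to-treat principle (Statistical analysis).

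**The concern.** The trigger is the kind of event, not a need to know the arm. Because disease exacerbation is placed within that kind, a poor efficacy course can qualify a patient for unblinding. If the granule works, exacerbations should be more frequent on placebo, so opened codes would be unequally spread between the arms and concentrated in patients who are doing badly. Those patients stay in the intention-to-treat comparison. DAS28 is clinician-assessed, and the Discussion concedes that most of the scores used to judge the disease rest on patients' subjective feelings. Any later rating made with knowledge of the arm could be biased, and the bias would be related to outcome.

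The block length is the lesser matter. With every block of length 4, and the length and permutations printed in the article, an opened code carries some information about the other three patients in its block.

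**Working it through.** **Step 1. The two sections side by side**

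| Question | Safety | Allocation and blinding |
|---|---|---|
| Is exacerbation of the patient's disease a serious adverse event? | Yes, it is the example given | Not addressed |
| Does a serious adverse event meet the code-break trigger? | Not addressed | Yes, with the Principal Investigator's consent |
| Must the allocation be needed for that participant? | Not addressed | Not a stated condition |

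Followed as written, exacerbation counts as a serious event, a serious event meets the trigger, and the code may be opened. The only gate is a consent with no criterion attached.

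**Step 2. The plan's own figure**

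Balanced blocks of length 4: 4!/(2!·2!) = 24/4 = 6. This agrees with the six permutations listed.

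**Step 3. What one opened code tells about a block-mate**

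Suppose one member is known to be in A. Three of the six permutations remain, and in two of them any given other member is in B. The chance of the opposite arm is therefore 2/3, against 1/2 with no information. In general, for block length b it is (b/2)/(b−1):

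- b = 4: 2/3 = 0.667
- b = 6: 3/5 = 0.600
- b = 8: 4/7 = 0.571

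One opened code determines nobody. Two opened codes fall in the same arm with probability 2/6 = 1/3, and then the other two members are known. Three opened codes fix the fourth.

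**Step 4. How often this matters**

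The article gives no rate of code breaks. Let p be the proportion of codes opened, assumed independent between patients and of arm.

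- An unopened patient has at least one opened block-mate with probability 1 − (1−p)³.
- That patient's arm is fully deducible with probability 3p²(1−p)·(1/3) + p³ = p².

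| p (assumed) | Codes opened of 340 | At least one opened block-mate | Arm fully deducible |
|---|---|---|---|
| 0.02 | 6.8 | 0.06 | 0.0004 |
| 0.05 | 17 | 0.14 | 0.0025 |
| 0.10 | 34 | 0.27 | 0.010 |
| 0.20 | 68 | 0.49 | 0.040 |

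Both probability columns presume that someone knows which patients share a block, that is, the order of entry within a stratum. If code breaks cluster in one arm, the figures would shift, because the independence assumption would fail.

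**The case against.** The strongest reply has five parts.

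1. **Consent is a real gate.** A reader might infer that every serious or unexpected event opens the code. The text does not say that. Opening needs the Principal Investigator's consent, each case goes to the ethics committee, and the second trigger is an unexpected adverse *reaction*, not any unexpected event. This stands. What remains is that no ground for consent is given, so the gate may let through exactly the cases of concern.
2. **Exacerbation is narrower than treatment failure.** A reader might infer that failing treatment is itself a trigger. It is not: nothing makes failure to improve, or failure to reach DAS28 below 2.6, a reason to unblind. The Safety phrase is also awkward, does not name RA, and could be read as covering other illness. In an RA trial, the patient's disease is most naturally RA, and the ambiguity is itself a reason to clarify.
3. **No contaminated rating is shown.** No section says that the DAS28 rater learns an opened code. Quality control has two investigators score each follow-up visit and averages them. Safety treats patients who need added RA treatment as off-cases, and Data management uses the last recording for those who withdrew, so some may have no rating after unblinding. This stands against any claim that the blind fails. It does not remove the risk, because nothing stated separates raters from opened codes.
4. **The block leak is weak.** The CRO holds the sequence, the strata are unnamed, and one code gives only 2/3. This stands. At p = 0.05-0.10 one could also say that 19-34% of blocks contain an opened code, from 1 − (1−p)⁴, but that sounds worse than the chance of deducing an arm. A reader might further infer that one opened code decodes the A/B split for the analyst. The split is released only after data lock, and no section says that the analyst knows any individual's opened code.
5. **An article condenses.** A full protocol may set out emergency unblinding in detail, so the absence of such detail is not the point here. The point is the rule that the two sections do state.

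**Conclusion.** The point holds in a limited form. As stated, worsening RA can by itself meet the code-break trigger, subject to a consent with no stated ground. Unblinding may therefore depend on outcome and differ between arms. That weakens the triple-blind claim for the patients affected; the documents do not support saying that it fails for the trial. How many patients are affected cannot be derived, because no rate of exacerbation or code-breaking is given.

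The block-length point is correct but secondary: a move from 1/2 to 2/3 per opened code, with full deduction at about 0.0025-0.010 under an assumed 5-10% opened. It rests on independent code breaks and on known order of entry within the stratum. The change is worth making because it is cheap and protects a clinician-assessed primary outcome.

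**What to change.** - Reconcile Safety with Allocation and blinding, so that it is explicit whether exacerbation means RA and so that efficacy worsening alone does not open the code.
- State that the Principal Investigator's consent depends on whether knowledge of the allocation is needed for that participant. Which events meet that test is a clinical judgement and is not proposed here.
- Let the CRO handle any unblinding required for reporting, and state that DAS28 raters and analysts do not learn opened codes.
- For allocations not yet used, have the CRO regenerate the list with randomly varied block lengths that are not disclosed to sites.

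**Cost.** Wording changes and a regenerated list. Longer blocks allow slightly more imbalance within a stratum: the largest possible difference between arms inside an open block is half its length, so 2 for length 4, 3 for length 6 and 4 for length 8.
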